**Methods/Design:**

This cluster randomized controlled trial will evaluate the feasibility and efficacy of FICare in six Chinese tertiary-level NICUs in China – three ‘intervention’ and three ‘control’ NICUs. The study steps are: (1) planning and preparation; (2) staff recruitment and training; (3) pilot study in two centers; (4) interim analysis and confirmation of sample size for main study; (5) implementation of main study; (6) data analysis and preparation and publication of study reports. The primary outcome measure is duration of hospital stay from admission to discharge. Secondary outcome measures are: (1) clinical outcomes, such as nosocomial infection, (2) weight gain, (3) breastfeeding, (4) time to full feed, and (5) maternal stress.

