### Hypotheses

The primary hypothesis is that the implementation of the FICare model for preterm infants in Chinese NICUs will result in a significant reduction in nosocomial infection and hence length of hospitalization. The secondary hypotheses are: (1) implementation of the FICare model in Chinese NICUs will improve maternal and infant outcomes including infant weight gain, maternal stress, and breastfeeding rates; (2) implementation of the FICare model in Chinese NICUs will result in decreased total medical expenses for preterm infants.

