### Setting and sample

In this multicenter cluster randomized control trial, six tertiary-level NICUs in three different cities (two NICUs in each city) will be randomized to two groups: FICare or control groups, such that the three NICUs in each group are from different cities. A total of 588 eligible infants (294 in each group, and 98 in each NICU) for whom parental consent has been obtained will be enrolled (the enrollment rate will be approximately 11 to 18 %). An internal pilot study will be first conducted in two NICUs, one from the FICare group and one from the control group. In all, 90 infants (45 from each NICU) will be recruited for the pilot study. The recruitment period of the pilot study will take around 10 months. It is estimated that 540 to 640 eligible infants (the estimated enrollment rate is approximately 21 to 25 %) are admitted to attending NICUs each year.

Patient inclusion criteria are:Infants are born at a gestational age of more than 28 weeks but less than 35 weeks;Infants have been receiving enteral feeds for more than 24 h; andInfants have vital signs that have been stable for more than 24 h. Patients must meet all three criteria.

Patient exclusion criteria are:Infant requires either invasive or non-invasive ventilation support;Infant requires surgical intervention;Infant is receiving palliative care;Parents have severe social issues or there is a language barrier;Infant is likely to be discharged within 1 week;Care-provider is not willing to commit to staying in the hospital for more than 6 h per day;Parents refuse to give consent; orInfant weighs less than 400 g at birth.

Patients, parents or care-givers meeting any one of these criteria should be excluded.

Patient discharge criteria are:Daily enteral feed is more than 160 ml/(kg day) and infants tolerate enteral feeding well;The infant has regained birth weight plus the body weight is more than 2 kg;Vital signs are stable;Neither intravenous medication nor oxygenation is needed;The baby gains weight for at least three consecutive days; andA car-seat test is passed if the parents drive.

Patients must meet all six criteria before being discharged home.

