The primary outcome measure is the total hospitalization period. The secondary outcome measures are: total medical expenses, infection incidence per 1000 hospitalization days, rate of breastfeeding, parental confidence and stress, assessment of feasibility and necessity of model of care, development of guidelines for supervising parents participating in the FICare model in the NICU.

The key independent variables are: rate of breast feeding, weight gain and growth speed, infection incidence per 1000 hospitalization days, total hospitalization period. The extra expenses for medical staff will include: salary for the hired research nurse, stipend for engaging doctors and nurses for extra hours of work related to the study (compared with the control groups), expenses for preparing parent education materials.

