### Data analysis

Data analysis will be conducted on an intention-to-treat basis. To take into account the clustering effect, Student’s *t* test adjusted for the inflation factor (or design effect) [11, 12] will be used, to compare the primary outcome between the FICare and control groups. Furthermore, a two-level hierarchical linear regression model will be used to compare the primary outcome measure between the two groups, accounting for patient-level characteristics, such as gestational age, small for gestational age, sex, Apgar score at 5 min, maternal age, delivery mode, maternal hypertension, chorioamnionitis, maternal education, and the NICU-level covariates (NICU size, number of nurses, and neonatologists). To take into account the cluster effect, a symmetric covariance matrix structure will be used for the models.

The secondary outcome measures will also be compared between the two groups using Student’s *t* test for continuous variables and the chi-square test for categorical variables adjusted for the inflation factor. A two-level hierarchical linear regression model or a logistic regression model, as appropriate, will be applied for the comparison of the outcomes between two groups, accounting for patient-level and NICU-level characteristics.

To assess the rate of growth for the two groups, we will further examine the rate of weight change over time, if applicable. Linear or nonlinear mixed-effect models for longitudinal data will be used to compare the rate of change in weight gain between the two groups, adjusted for duration of hospital stay, and patient-level and NICU-level characteristics. An interim analysis for the internal pilot study will first be conducted using similar methods, if applicable. The preliminary results will then be used to re-justify the sample size, using the method of Lake et al. [10].

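### The supplementary growth model adjusts the arm comparison for duration of hospital stay, a post-randomisation variable that is the primary outcome and depends partly on weight gain

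*Protocol article*

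**What the plan says.** The third paragraph of Data analysis adds, where applicable, an examination of weight change over time. On the type of model it states: "Linear or nonlinear mixed-effect models for longitudinal data will be used". The aim of this modelling is given as "to compare the rate of change in weight gain between the two groups, adjusted for duration of hospital stay", with further adjustment for characteristics of the infants and of the NICUs. It gives no reason for including stay and describes no version of this model without it.

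Four other places bear on that covariate:

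- **Data collection procedures:** "The primary outcome measure is the total hospitalization period".
- **Sample size calculation:** mean stay is 28 days with SD 15, and FICare is expected to reduce it by 5 days.
- **Setting and sample, discharge criteria:** two of the six conditions, all of which must be met, concern weight. One is "The infant has regained birth weight plus the body weight is more than 2 kg". The other reads "The baby gains weight for at least three consecutive days".
- **Abstract and Hypotheses:** weight gain is a secondary outcome ("2) weight gain, (3) breastfeeding, (4) time to full feed, and (5) maternal stress"), and the secondary hypothesis is that FICare "will improve maternal and infant outcomes including infant weight gain, maternal stress, and breastfeeding rates".

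**The concern.** A covariate in a treatment comparison should not itself be changed by the treatment or by the outcome being modelled. On the protocol's own account stay is changed by both: FICare is meant to shorten it, and an infant who grows faster reaches the discharge weight sooner. Adjusting for it compares FICare infants with control infants who happened to stay equally long, and randomisation does not make those groups alike. Analysing by intention to treat does not help, because the problem is the covariate and not the analysis set.

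At stake is the reading of a named secondary hypothesis. Depending on the form of the model, the adjustment could shrink a real growth benefit or produce an apparent loss where there is none.

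**Working it through.** The protocol gives no figure for the growth comparison, so there is none to reproduce. The check has three parts.

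**1. Structure.** Let W be weight at entry (g), g the daily gain and S the stay. The weight criterion makes stay roughly

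S = (2000 - W)/g + other delays.

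For given W and delays, S falls as g rises. Holding S fixed therefore restricts g, which is the quantity being compared.

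**2. Regression of each infant's daily gain on arm and stay.** In a linear model,

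adjusted effect = true effect - b × (effect of arm on stay),

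where b is the slope of daily gain on stay within arms.

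Assumed inputs, not from the documents: entry weight 1600 g (SD 150), gain 25 g/day (SD 5), stay = 7 days + days to reach 2 kg + random delay. The delay SD is set at 2 days (control-arm stay SD about 7.8) or 12.5 days (stay SD about 14.5, close to the protocol's 15).

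| Scenario | No stay term | With stay, SD of stay about 7.8 | With stay, SD about 14.5 |
|---|---|---|---|
| True effect 0; stay cut 5 days by other routes | 0.0 | -1.5 | -0.45 |
| True effect +3 g/day, acting on stay only through weight | 3.0 | 2.4 | 2.84 |

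The formula explains these results. The first row implies b = -1.5/5 = -0.30 and b = -0.45/5 = -0.09. In the second row, at mean values, stay falls by 400/25 - 400/28 = 16.0 - 14.3 = 1.7 days. That gives 3 - 0.30 × 1.7 = 2.5 and 3 - 0.09 × 1.7 = 2.85, close to the simulated values.

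Adding entry weight as a covariate makes the bias larger in the tight case (-4.2 to -4.4 for a true 0; 1.2 for a true 3). With the wider spread it changes little (-0.55 and 2.80).

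A second assumed set used entry weight 1500 g (SD 200), gain 20 g/day (SD 5), a true +4 g/day and entry weight as a covariate. Stay fell by 5.0 days. The estimate was 4.0 without stay and 1.4 to 2.6 with it, although stay had an SD of 12.6 to 14.5 days. So the SD of stay does not fix the bias on its own; what matters is how much of that spread comes from growth.

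**3. Repeated-weights model, the type the protocol names.** Random intercept and slope, first set of inputs with delay SD 2, 588 infants, weights every 2 days, 8 runs, clustering omitted. Group difference in slope, g/day:

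| True effect | No stay term | Stay as main effect | Stay also acting on the slope |
|---|---|---|---|
| 0 (stay cut 5 days) | 0.02 | -0.05 | -1.50 |
| +3 | 3.00 | 2.95 | 2.34 |

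A smaller run under the second set (true +4, a further 3-day cut in stay by another route, 4 runs, standard error 0.3 to 0.4) gave 4.1, 3.8 and 2.0: the same pattern.

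**The case against.** Four points can be made for the protocol, and most of them limit the concern.

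- **Scope.** A reader might infer that every weight-gain comparison is biased, or that the primary analysis is. The documents do not support that. Secondary outcomes are first compared by t tests adjusted for the inflation factor, then by two-level models, and stay is not named as a covariate in either. The primary analysis does not condition on stay. The affected model is an addition, planned only where applicable.
- **Model form.** A reader might infer that bias is certain. If stay is only a main effect, the slope contrast hardly moves, and an article may leave that detail to an analysis plan. This stands as a limit on size. It is no reason to keep the term, which in one form does almost nothing and in the other distorts the result.
- **Size.** The largest value above, about -4.4 g/day, needs a stay SD of about 7.8 days against the protocol's 15. It should not be quoted as the expected error.
- **The list of variables.** "The key independent variables are: rate of breast feeding, weight gain and growth speed, infection incidence per 1000 hospitalization days, total hospitalization period" could be read as a plan to use outcomes as regressors. It stands in a data-collection section, fits no model, and apart from stay in the growth model none of its items appears among the named covariates. It is best read as a labelling slip.

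The remaining defence is that infants are observed for different lengths of time. A mixed model with time as a variable accommodates unequal follow-up, and a daily rate already standardises for it.

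**Conclusion.** The point holds for the supplementary growth model. The protocol names a covariate that is affected both by treatment and by the outcome being modelled, so the adjusted contrast is not a randomised comparison.

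The bias is near zero for the slope contrast if stay is a main effect only. If stay acts on the slope, or in a per-infant daily-gain regression, the first set of inputs gives about -0.5 to -1.5 g/day under no true effect with stay cut 5 days by other routes, and about 2.4 to 2.9 for a true 3 g/day. The smaller bias in each range comes from the daily-gain regression with stay spread close to the protocol's SD of 15; the slope form was run only with the narrower spread. Entry weights, growth rates and delays are all assumed, and the second set shows that the proportion lost can be greater. The direction is more secure than the size.

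The primary analysis, the sample size and the other secondary comparisons are not affected. The point should be corrected, but it does not threaten the trial's main conclusion.

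**What to change.** Delete duration of hospital stay from the covariates of the growth model. Estimate the arm-by-time contrast from the repeated weights, adjusting only for pre-enrolment patient characteristics (including weight at enrolment or birth weight) and the NICU characteristics already listed. If a stay-adjusted version is kept, label it exploratory and state how stay enters.

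Two further changes are optional: a sensitivity analysis restricted to a fixed early window after enrolment, to address discharge that depends on weight, and relabelling the list of key independent variables as outcomes, which is editorial.

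The cost is analysis wording only, with no change to sample size. Under Trial status the main study was still in progress, so at that stage the change could be made before the final analysis.

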### Ethical approval and trial registration

The study received ethical approval from the ethics committee of the Third Xiangya Hospital of Central South University for Clinical Research. The ethical approval number is (2013) Ethic_CSU(S123). The study has been registered in Chinese Clinical Trial Registry (registration number, ChiCTR-TRC-14004736). Informed consent has been obtained from each participant.

In addition, the following procedures were taken to ensure compliance with ethical standards:To obtain informed consent from each participating parent before enrollment;To set up a system for incidence reporting, including the use of time limitations (less than 24 h) and the need for a formal written report;To use patient numbers instead of patient names when summarizing data;To obtain parents’ written approval for publishing their names or pictures on the research update;To respect parents’ decisions to join or leave the study at any time.

### Quality control procedures

Quality control procedures include:Training participating nurses in the study carefully before enrolling parents;Delivering parent education lectures regularly and offering daily bedside supervision to parents;Hiring a full-time research coordinator to oversee the project and research nurses at each site to collect the data;Periodically distributing a research update to each participating NICU, and collecting feedback from each NICU.

In addition, the principle investigator will routinely work on the analysis of enrollment and completion numbers and feedback from parents or nurses, work with statistical specialists and discuss the progress of the study with the co-principle investigator.

## Discussion

This study is, to our knowledge, the first cluster randomized control trial to study the feasibility and cost-effectiveness of FICare in China. As in most NICUs in China, parents are not allowed to enter into the NICU ward. By establishing that FICare is a practical model of NICU care for stable preterm infants in China, this project will have a significant impact on health outcomes, medical practice and policy, and the cost of medical care.

In China, the One-Child Policy has been in place for more than three decades. Most young parents are themselves each an only child and as such may lack experience in taking care of newborn infants, which is often gained in families with multiple children through taking care of younger siblings. With changing migration patterns, new parents may also lack family support. A recent Chinese study [13] reported that mothers experience a lot of anxiety when their newborn infants are taken from them to the NICU, that breast milk secretion significantly decreases and that most parents really want more time to visit their infants. In addition, 84.2 to 96.4 % of Chinese parents wanted to learn how to take care of their newborn infants from medical professionals [14].

In Western countries, in response to this problem, many NICUs have adopted models of family-centered care in their units. This reflects a shift from the traditional focus on the biomedical aspects of an infant’s condition to a concern with seeing infants in the context of their families and recognizing the primacy of family in an infant’s life. No matter whether the infant is a preterm or a term baby. Consistent with this philosophy, many NICUs in the Western world have adopted more ‘baby-friendly’ environments and procedures, including minimizing stimulation, providing developmental care, encouraging skin-to-skin contact with parents, dimming the lights and reducing noise levels [15]. The scientific literature shows that there is both theoretical and real benefit for infants if parents are more involved in their care, especially in terms of reducing length of hospital stay [16, 17] and improving weight gain [8, 18].

China is a large country with 30 provinces, each with varying economic status, a factor that may have a significant influence on the outcomes of infants in the NICU. In addition, we do not want to conduct this study in a NICU with too many beds, as it may be difficult to maintain the quality of the study in a larger NICU, particularly in terms of problems with human resources, such as varying availability of nurses or inconsistent shift patterns. Our main objective during our baseline research was to collect data on Chinese NICUs, including the number of NICU beds, mean birth weight of patients, percentage of preterm babies, percentage of babies with gestational age <32 weeks, nurse–patient ratio, mean hospitalization period, total medical expense per patient, top three reasons for early discharge home, re-admission rate within 30 days after discharge, and possibility of allowing parents to enter NICU (0 = impossible, 1 = probable, 2 = very possible, 3 = already allowed). As a result of our analysis we identified and recruited six NICUs at the same academic level from three provinces, all from cities with an above-average economic level. The NICUs are all similar in size and have a similar patient mix. Thus, we have tried to ensure that program implementation will be as consistent as possible across the six sites with fewer barriers linked to economic status and availability of hospital and parent resources. Following success in this study we will be able to expand the program to examine whether it is feasible in regions with a lower economic status and more financial challenges.

We estimate that there will be a drop-out rate of approximately 10 % of families who enroll in the study, mostly owing to financial issues or time constraints. To minimize the effect of the biases this could introduce, we will conduct analysis with an intention-to-treat basis. There are limitations to this study. Unlike a randomized controlled trial, where patients are randomized rather than centers, some potential confounders, such as sex, gestational age, or birth weight, cannot be complete controlled for. To minimize the biases that may exist between two centers because of this, we will use multilevel models to compare the outcomes between two groups adjusting for these potential confounders in the analysis stage. We will also adjust the analysis for any potential confounders due to differences in the NICUs (NICU size, number of nurses, and neonatologists). Since the eligible infants in a NICU cannot be identified before randomization, i.e., consent cannot be obtained before randomization, this could introduce a selection bias. To minimize this bias, we will ensure that the recruitment of infants is conducted by a research coordinator who is blind to group allocation.

The project proposed here will take the principles of the FICare model as described by the Mount Sinai Hospital group and see how they can be applied to Chinese NICUs and what the outcomes are. The key pillars of this project are [8]:Mothers or close family members are present in the NICU to take care of their newborn infants and collaborate with the NICU medical team in the infant’s care;Parent education is provided, such that parents can truly participate;Infant holding and parents being present at their infant’s bedside is supported by unit policies, physical, and environmental supports;Nurses are provided with tools and education to enable families to be part of the care team; andThe entire care team supports the model of care.

The project is a multicenter cluster randomized controlled trial and is not a technology-based project. The approach used in this project could be transferable to many other areas of medical care, such as pediatrics, chronic care, and geriatrics. Data in this project can be used to inform health policy in NICUs across China so that parents can be allowed to enter the NICU and be at their infant’s bedsides during baby’s hospitalization, and modifying the design of NICUs in China to facilitate the participation of parents in caring for their newborn infants.

### Trial status

The study began in April, 2014, and patient enrollment commenced in July 2014. The internal pilot study was completed by the end of May, 2015. The study is in the stage of the main study. Official registration was completed in May, 2014. The registration number of the study is ChiCTR-TRC-14004736. The whole study is scheduled to be completed by the end of December, 2016.

## Abbreviations

FICare: family integrated care
NICU: neonatal intensive care unit
SNAPPE-II: Score for Neonatal Acute Physiology–Perinatal Extension-II
